## Introduction

Severe acquired brain injury (sABI) is characterized by traumatic, anoxic, vascular, or other brain damages that cause coma for at least 24 hand frequently lead to permanent sensorial, motor, cognitive, or behavioral disabilities. The incidence rate of sABI patients is estimated between 10 and 15 new cases/100,000 persons/year and the prevalence rate between 300 and 800 cases /100,000 persons, which represents comprehensively about 150,000 persons in 2016 in Italy (1, 2).

After sABI, some patients may survive in a state of prolonged disorder of consciousness (DoC) (3), a condition that encompasses (1) unresponsive wakefulness syndrome (UWS), in which the eyes are open, but there is no evidence of voluntary behaviors and (2) minimal consciousness state (MCS), an intermediate state in which minimal, inconsistent but reproducible behavioral signs of responsiveness are present (4). Based on the complexity of patients' behavioral responses, a subcategorization of MCS patients was proposed (5); namely, “MCS minus” (MCS–) characterizes patients with intentional low-level behavior, such as visual search or localized motor response to nociceptive stimulus, and “MCS plus” (MCS+) indicates patients with high-level behavioral interactions, such as execution of simple verbal commands (5). In some cases, patients recover full consciousness, as marked by the regaining of functional and reliable “yes/no” communication (emergence from MCS, E-MCS), but they may still present severe motor and cognitive or behavioral impairments persisting lifelong.

Besides the severity of the neurological state, patients with sABI frequently present a high clinical complexity characterized by very frequent comorbidities (6) and medical complications (7), which can further impact clinical improvement and survival. Although late consciousness recovery and progression have been reported in patients with UWS or MCS (8), long-term mortality is high (42–52%) in patients with prolonged DoC (1, 2), and survivors frequently show severe to extremely severe outcomes (9).

Younger age, shorter postevent time, and traumatic etiology have been identified as the possible clinical predictors of short-term consciousness recovery in patients with prolonged DoC (10).

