### Outcome Measures

The primary outcome is the functional recovery, given by the achievement of a moderate functional disability (GOS-E>4), whereas the independent variables will be the severity of the patients' clinical state at admission. For those patients who will remain in DoC at discharge from the IRU, given that the GOS-E does not allow accurate discrimination between different states of consciousness, consciousness improvement will be considered. The improvement will be stated as the transition from one state of consciousness to a higher one (based on the CRS-R assessment). These outcomes will be measured both at short-term evaluations, T1 and T2, and at long-term ones, T3 and T4.

Secondary outcomes will be considered at the same time points. They are (1) tracheostomy decannulation success and its timing and (2) complete oral feeding recovery corresponding to FOIS score ≥4. Additionally, at follow-up time points (T3 and T4), the level of participation, using the CIQ scale, and the subjective and caregiver perceived QoL, using the QoLibri, will also be considered as secondary outcomes.

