The recovery of consciousness for patients with a DoC is the first rehabilitative goal and one that largely conditions subsequent objectives. Identifying the prognostic factors of consciousness improvement needs a correct diagnosis of consciousness upon admission to the IRU. More and more literatures were provided in the last few years to support diagnostic decisions on DoCs, but the evidence remains insufficient, given the complexity and the ethical weight of the issue. The CRS-R scale has been recommended by the Congress of Rehabilitation Medicine for the clinical assessment of consciousness levels in patients with DoC (41). However, several potential confounding factors related to examiner, patient, and environment could hamper the clinical diagnosis, and it has been estimated that up to 40% of noncommunicating patients with DoC may be wrongly classified (42). Along with the fluctuation of the consciousness level itself, some concomitant clinical states, such as aphasia, apraxia, object, or visual agnosia, marked spasticity (43), and hyper or hypotonus was reported to produce impossible or improbable CRS-R scores (44). Additionally, some associated pathologies or clinical conditions, such as the presence of a CINMP (22) or the presence of tracheostomy (45, 46), may limit the recognition of voluntary behavior and, consequently, hinder a correct diagnosis of consciousness (42). This risk of misdiagnosis has serious ethical concerns and deep implications for medical management and the decisions of the patient' families (47). For the same purpose, sophisticated diagnostic techniques such as functional magnetic resonance imaging (fMRI) and positron emission tomography (PET) have been developed (48). By detecting volitional activity, not recognizable on clinical grounds, they provide a more robust evaluation of consciousness, having, in addition, the advantage to provide useful prognostic information. Besides these technologically advanced tools, which are unsuitable for large-scale use, since they are sophisticated, expensive, and time-consuming, some studies investigated the diagnostic and prognostic value of widely used and easily repeatable instrumental approaches (e.g., standard clinical EEG, ENG/EMG, or evoked potentials) (15, 18, 19). Both the European Academy of Neurology and the American Academy of Neurology have recently recommended the use of a multimodal evaluation by combining clinical evaluation, EEG, SEP, and functional neuroimaging for improving clinical classification and prognostication of people with DoC (49, 50). However, a broad consensus on diagnostic and prognostic procedures for the clinical care of individuals with prolonged DoC has not been reached, yet. Indeed, a recent international survey showed that diagnostic and prognostic procedures for DoC are still extremely variable across geographic regions worldwide (37). In the present work, for greater accuracy of diagnosis, it was planned to perform a multimodal consciousness diagnosis by the integration of clinical evaluation (through the CRS-R) with specific EEG patterns related to consciousness (19).

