
To identify a profile of sABI patients based on a multiparameter assessment, the combination of the many recorded measures can be best exploited by machine learning analysis. The applicability of these solutions is also supported by the consideration that, with the only exception of the neurogenetic assessment, all the clinical and instrumental variables selected in this study are easily exportable to other clinical realities because of their low cost and high feasibility. Specifically, in this context, an accurate prediction is relevant both for planning a personalized rehabilitation pathway and for communication with relatives and caregivers. For these reasons, the ultimate goal of this study is to reliably predict the main recovery milestones, including the achievement of a consciousness recovery, tracheostomy decannulation, complete oral nutrition, functional independence, and the recovery of participation in familiar and social contexts. Differently from what is most often found in the existing literature, the aim of these analyses will be two-fold, addressing both the success in the achievement of these goals and their timing. The candidate predictors of these solutions will be selected from a comprehensive evaluation of sABI patients, including the biomarkers obtained from genetic sequencing and quantitative and qualitative EEG features.

Finally, another innovative point will be the comparison of these models with the clinical assessment performed by a multidisciplinary team within the first 2 weeks from admission. This comparison will represent a first step in the direction of computational tools translation into clinical practice.

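### Consciousness improvement is defined only in patients still in DoC at discharge, so patients who emerged by then are left out of the outcome

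*Protocol article*

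**What the plan says.** Outcome Measures opens with the primary outcome: "The primary outcome is the functional recovery, given by the achievement of a moderate functional disability (GOS-E>4"). No discharge condition is attached to it. The same paragraph, before the secondary outcomes are listed, introduces a consciousness outcome for a subgroup: "For those patients who will remain in DoC at discharge from the IRU, given that the GOS-E does not allow accurate discrimination" between states of consciousness. It then defines improvement: "The improvement will be stated as the transition from one state of consciousness to a higher one (based on the CRS-R assessment"). On timing it says "These outcomes will be measured both at short-term evaluations, T1 and T2, and at long-term ones, T3 and T4".

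The Introduction supplies the scale. Prolonged DoC is "a condition that encompasses (1) unresponsive wakefulness syndrome (UWS") together with MCS. Above these stands full consciousness, labelled "emergence from MCS, E-MCS), but they may still present severe motor and cognitive or behavioral impairments persisting lifelong". E-MCS is therefore outside DoC.

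The Discussion gives the purpose. "The recovery of consciousness for patients with a DoC is the first rehabilitative goal", and the milestones to be predicted are listed as "including the achievement of a consciousness recovery, tracheostomy decannulation, complete oral nutrition" and others. The closing paragraph of the Discussion again names prognostic markers of consciousness recovery as an aim. The secondary outcomes contain no other consciousness endpoint.

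**The concern.** The subgroup is formed by what happens after admission, on the scale that the outcome measures. Someone who moves from UWS to MCS and stays there is in the subgroup and can count as improved. Someone who moves from UWS to E-MCS before discharge is not in it and gets no credit for consciousness; if that person's GOS-E is 4 or lower, the only outcome left records a failure.

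Two things are at stake. First, the improvement rate and the predictor effects would be estimated after the patients with the largest gains have been removed. Second, a prognostic model is meant for use at admission, when nobody knows who will still be in DoC at discharge. A model fitted in this subgroup has no identifiable target population at the time of use.

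**Working it through.** **The plan's own figure.** Study Design and Participants sizes the study on GOS-E: favourable outcome in 3% (UWS) and 47% (MCS), uncertainty 3% and 5%, significance level 0.05 (two-sided assumed). With n = z²p(1−p)/d²:

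- MCS: 1.96² × 0.47 × 0.53 / 0.05² = 382.8, so 383 (stated 384).
- UWS: 1.96² × 0.03 × 0.97 / 0.03² = 124.2, so 125 (stated 125).

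Both reproduce. The sizing contains no discharge condition, so it is not touched by this point.

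**What follows from the definitions alone.** Take the states in order: UWS, MCS, E-MCS. The subgroup at discharge is UWS or MCS.

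- Admitted in MCS: the only higher state is E-MCS, which takes the patient out of the subgroup. Improvement by discharge is impossible.
- Admitted in UWS: only UWS to MCS can count. UWS to E-MCS is excluded.
- If MCS−/MCS+ subcategories are used, MCS− to MCS+ can also count. Outcome Measures does not say whether they are.
- Patients who emerge after discharge remain in the subgroup and can count at later visits: T3 and T4, and T2 if discharge came earlier.

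MCS is the planned group of 384 out of 384 + 125 = 509, or 75%.

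**Illustration 1: rates.** The documents give no transition rates, so these are assumed, with assessment at discharge.

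- Low case: UWS to MCS 30%, UWS to E-MCS 5%, MCS to E-MCS 20%. Improvers among all admitted in DoC: 125 × 0.35 + 384 × 0.20 = 120.6, or 23.7% of 509. Still in DoC: 125 × 0.95 + 384 × 0.80 = 426.0. Improvers among them: 125 × 0.30 = 37.5, or 8.8%. Share of improvers left out: 1 − 37.5/120.6 = 69%.
- High case: 40%, 20%, 60%. Improvers: 125 × 0.60 + 384 × 0.60 = 305.4, or 60%. Still in DoC: 125 × 0.80 + 384 × 0.40 = 253.6. Improvers among them: 125 × 0.40 = 50, or 19.7%. Left out: 84%.

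**Illustration 2: odds ratio under proportional odds.** Assume a balanced two-level predictor, log odds ratio 1 (odds ratio 2.72), and outcome levels no change, improved within DoC, emerged. Let e0 and e1 be the emergence probabilities at the two predictor levels. After emerged patients are dropped, the odds ratio becomes 2.72 × (1 − e1)/(1 − e0). The assumed share improving within DoC cancels out.

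| Emerged by discharge | e0 | e1 | Odds ratio in subgroup |
|---|---|---|---|
| 30% | 0.198 | 0.402 | 2.72 × 0.598/0.802 = 2.03 |
| 50% | 0.378 | 0.622 | 2.72 × 0.378/0.622 = 1.65 |
| 60% | 0.483 | 0.717 | 2.72 × 0.283/0.517 = 1.49 |

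**Illustration 3: without proportional odds.** UWS patients only, assumed probabilities of reaching MCS and E-MCS.

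| Predictor present (MCS, E-MCS) | Predictor absent (MCS, E-MCS) | Odds ratio, all | Odds ratio, subgroup |
|---|---|---|---|
| 25%, 30% | 25%, 5% | 2.85 | 1.56 |
| 30%, 30% | 25%, 5% | 3.50 | 2.10 |
| 20%, 40% | 30%, 10% | 2.25 | 1.00 |

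In the last row the comparison in the subgroup is 0.20/0.60 against 0.30/0.90, both one third, so the predictor disappears.

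**The case against.** A reader might infer that the primary analysis as a whole is conditioned on its own result. The text does not support that. GOS-E>4 carries no discharge condition, the Statistical Analysis section builds the primary regressions on GOS-E, and the sample size rests on GOS-E. Emerged patients stay in all of these.

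A reader might also infer that the two definitions are merged into one endpoint, with GOS-E scored in some patients and CRS-R in others. Nothing says so. Consciousness improvement is only to be considered in the subgroup, and the next sentence speaks of outcomes in the plural, which fits an added outcome. Replacement is not ruled out either, and that ambiguity is a fair criticism in itself.

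Nor is it true that everyone who emerges is lost: those who emerge after discharge can count later. The rates in Illustration 1 take discharge as the assessment time and do not represent the long-term visits.

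Finally, the Discussion lists consciousness recovery as a prediction milestone without repeating the restriction, so the machine-learning work may include emerged patients, and Statistical Analysis names no regression in the discharge subgroup. This stands as far as it goes. But Outcome Measures holds the only definition of a consciousness endpoint in the article, and an analysis that follows it inherits the selection. Because the article states the population outright, this is not detail left to an analysis plan.

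**Conclusion.** The point holds for the consciousness component only. As written, its population is selected on a post-admission state of the outcome itself, it leaves out patients who emerged by discharge, and it conflicts with the stated aim of predicting consciousness recovery. The impossibility of improvement by discharge for patients admitted in MCS follows from the definitions, provided MCS−/MCS+ subcategories are not used.

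The size of the distortion is not known. Under the assumed rates, 69–84% of improvers by discharge are left out, and an odds ratio of 2.72 shrinks to between 2.03 and 1.49. The shrinkage requires a predictor that raises the chance of emergence; it is not a result from the trial's own figures. GOS-E>4, its regression and the sample size are unaffected. Whether consciousness improvement replaces or supplements GOS-E in the subgroup is unclear and should be stated.

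**What to change.** In Outcome Measures:

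- Delete the restriction to patients still in DoC at discharge.
- Define consciousness improvement in all patients in UWS or MCS at T0, as a transition from the T0 state to a higher one, with E-MCS as the top state, at the planned visits T1 to T4. State whether MCS− and MCS+ count as separate states.
- Say how deaths are handled, for example as a separate category. This is a choice for the trial team.
- Keep GOS-E>4 for the whole cohort, state that consciousness improvement is an additional outcome, and report the two separately.

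Table 1 already schedules CRS-R at T0 to T4 (T3 and T4 as phone follow-up), so no new data collection is needed. The cost is wording and a little analysis.

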
After regaining consciousness, patients with sABI often present many factors that may limit their recovery. Indeed, significant neurological impairments, including motor deficits, myoclonus, dystonia, movement disorders, aphasia, neglect, abulia, impairments in attention, memory, executive functions, mood disorders, and epileptic seizures, may have a dramatic impact on the level of functional independence and quality of life (51). Also, sABI patients frequently present a high clinical complexity, with a high rate of comorbidities (6) and medical complications (7) that can further compromise the functional prognosis. For their complex nature, patients with sequelae of sABI require several assessment instruments to correctly quantify every residual symptom and adequately reflect their clinical state during the acute, postacute, and community-living sABI phase. Furthermore, given the long duration of the rehabilitation process and the continuous evolution of patients over time, the measurement of outcomes also needs to be dynamic, to accurately depict, as realistically as possible, the patient's situation at each time point. Recently, the Italian Society of Physical and Rehabilitation Medicine proposed a minimum assessment protocol for post-sABI patients (52); however, there is no National Health System (NHS) requirement as to the measures of sABI rehabilitation outcomes. In this study, evaluation tools were chosen in accordance with the Italian Society of Physical and Rehabilitation Medicine minimum assessment protocol (52), and targeted outcome measures were hierarchically organized based on the patient's state of consciousness. Only after the consciousness recovery, some measures of functioning, including motor and cognitive impairment, activity, and participation were applied. Further, special attention was given to the care burden (the presence of compliances and comorbidities, the presence of medical devices, oral/artificial feeding, and communication capabilities) to assess the impact, on both the caregiver and the NHS, at discharge and until 24 months after the acute event.

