In conclusion, this study aims to identify reliable prognostic markers of consciousness recovery, functional autonomy, and participation level in the late-acute and chronic phase after sABI. In addition to the classical multivariate logistic regression analysis, advanced machine learning algorithms will be crossvalidated to obtain data-driven prediction models and allow stratification into subgroups of patients with a high or low probability of recovery. The development of such predictive models aims at helping clinicians and patients' families to plan personalized treatment strategies in terms of intensity, duration, and protocols of a comprehensive rehabilitation program and to make appropriate decisions regarding treatment and care. Finally, it should be noted that patient profiling will include measures and procedures that are easily available at the patient's bedside, with affordable time, resources, and money to determine a real impact on the NHS and to optimize the use of resources.

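### The consciousness outcome (any upward CRS-R step, only in patients still in DoC at discharge) does not match the consciousness-recovery milestone that the models are meant to predict

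*Protocol article*

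**What the plan says.** **Outcome rule.** In the protocol article, Outcome Measures makes GOS-E>4 the primary outcome and adds a consciousness outcome for one subgroup: "For those patients who will remain in DoC at discharge from the IRU". The reason given is that GOS-E cannot separate states of consciousness well. The event is then defined: "The improvement will be stated as the transition from one state of consciousness to a higher one (based on the CRS-R assessment". Both outcomes are to be measured at T1 to T4.

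**Prediction target.** The Discussion says of the machine-learning work that "the ultimate goal of this study is to reliably predict the main recovery milestones, including the achievement of a consciousness recovery". Its closing paragraph says that "this study aims to identify reliable prognostic markers of consciousness recovery, functional autonomy, and participation level". Neither place defines *consciousness recovery* or refers back to Outcome Measures.

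**What recovery appears to mean.** The Introduction says that "some patients may survive in a state of prolonged disorder of consciousness (DoC" and lists UWS and MCS as the two conditions within it. It then describes a further group in which "patients recover full consciousness, as marked by the regaining of functional and reliable “yes/no” communication (emergence from MCS, E-MCS". The Discussion, explaining how the assessments are ordered, says: "Only after the consciousness recovery, some measures of functioning, including motor and cognitive impairment, activity, and participation were applied". Here recovery works as a threshold that a patient passes.

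**The concern.** The event that would be scored and the milestone that would be reported seem to be different things, in different patients. The scored event can be met by someone who remains in DoC. It is also assessed only in patients chosen by their state at discharge, which is itself a result of the course being predicted.

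Two things are at stake. First, the article intends these predictions for talking with relatives and for decisions on treatment and care. A probability described as recovery of consciousness should not rest on patients who are still in DoC, nor leave out those who emerged early. Second, the study is about baseline predictors. Conditioning on a post-baseline state that depends on recovery can distort the apparent effect of baseline state and of anything correlated with it, such as the admission CRS-R score.

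**Working it through.** **1. The plan's own figures, and what they cover.** The only computed sizes are in Study Design and Participants. The single-proportion precision formula, n = z² p(1−p)/d² with z = 1.96, gives:

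- UWS, p = 0.03, d = 0.03: 3.8415 × 0.0291 / 0.0009 = 124.2, so 125 (stated 125).
- MCS, p = 0.47, d = 0.05: 3.8415 × 0.2491 / 0.0025 = 382.8, so 383 (stated 384; p = 0.50 gives 384.1).

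The sizes reproduce to within one patient. They concern GOS-E>4. Neither the rates nor the margins describe a change of state on the CRS-R, so they cannot be used to size this point.

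**2. Who is scored, and how.** Assume that the states are UWS < MCS < E-MCS and that change up to discharge is judged against the state at T0. DoC means UWS or MCS.

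| State at T0 | State at discharge | In the outcome's population? | Counts as improvement? | Left DoC? |
|---|---|---|---|---|
| UWS | UWS | yes | no | no |
| UWS | MCS | yes | **yes** | no |
| UWS | E-MCS | no | not scored | yes |
| MCS | UWS | yes | no | no |
| MCS | MCS | yes | no | no |
| MCS | E-MCS | no | not scored | yes |

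At discharge, the only cell scored as a success is UWS to MCS, where the patient is still in DoC. Both cells in which the patient has left DoC are outside the population. Up to that point, scored improvement and emergence have no patients in common.

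**3. Effect on the baseline predictor.** Among patients in UWS at T0, let u1 be the share in MCS at discharge and u2 the share who have emerged. Among patients in MCS at T0, let m be the share who have emerged.

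| Definition, at discharge | Rate, UWS at T0 | Rate, MCS at T0 |
|---|---|---|
| As written (still in DoC at discharge) | u1 / (1 − u2) | 0 / (1 − m) = 0 |
| Any upward step, all in DoC at T0 | u1 + u2 | m |
| Emergence, all in DoC at T0 | u2 | m |

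As written, the UWS rate is at least as high as the MCS rate whatever the data show, because the MCS rate is fixed at zero. Under the emergence definition the difference is u2 − m, which can take either sign.

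**4. After discharge.** Patients in DoC at discharge may still emerge by a later assessment, so the fixed zero applies only up to discharge. The selection remains: patients who emerged during the stay are missing from the consciousness outcome at T3 and T4 as well. The article does not say how T1 and T2 fall relative to each patient's discharge.

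**5. Size.** The article gives none of u1, u2 and m, nor the number expected to be in DoC at discharge. The shift in event rates cannot be computed.

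**The case against.** The strongest reply is that Outcome Measures holds the only operational rule and calls it improvement, while the Discussion uses recovery loosely for the same thing. The Discussion does pass from recovery of consciousness to prognostic factors for its improvement as one subject, and the aim at the end of the Introduction names functional recovery only. The Introduction's sentence on emergence is background and speaks of full consciousness. The rule also has a sensible purpose: to register gradations that GOS-E misses in patients who stay in DoC. Those who emerge are still scored on GOS-E.

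Much of this stands, and it rules out several stronger readings that a reader might infer:

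- *The plan has two conflicting success rules, with UWS to MCS a success under one and a failure under the other.* No section scores that change as a failure. The reading depends on carrying the Introduction's account of full consciousness into the Discussion.
- *MCS– and MCS+ create a third event set.* The Introduction presents them as a subdivision of MCS, and nothing makes them separate states for this outcome.
- *The effect can be sized as a share of the 125 UWS patients and set against the 3-point margin.* Those 125 are not the outcome's denominator, and the margin belongs to GOS-E.

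The loose-label defence does not remove the problem. The Discussion's statement that functioning measures follow recovery of consciousness treats it as a threshold. Even if the two terms were synonyms, the restriction to patients in DoC at discharge would still exclude those who emerge earlier and would still fix the zero shown in the working. Nor is this a detail that an article leaves to a fuller document: the population and the event are both stated.

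**Conclusion.** The concern holds in this form: the consciousness outcome, as populated and defined, does not correspond to the milestone that the models are said to predict. Followed literally, it builds in a comparison by baseline state that favours UWS up to discharge. This goes beyond wording and should be changed, though it does not affect the GOS-E outcome or the sample size.

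The conclusion rests on three assumptions. The states are UWS, MCS and E-MCS. Change up to discharge is judged from T0. *Consciousness recovery* means leaving DoC, which the Introduction and Discussion suggest but do not state. If MCS– and MCS+ were separate states, a patient in MCS– at T0 could improve within DoC, but one in MCS+ still could not. The mismatch in population does not depend on how the states are listed.

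The direction of the distortion up to discharge follows from the definition. Its size is unknown.

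**What to change.** In Outcome Measures:

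- Define the population for the consciousness outcomes as patients in DoC at T0, whatever their state at discharge.
- Keep any upward CRS-R transition as *consciousness improvement*. List the states in order, say whether MCS– and MCS+ are separate, and report results by baseline state or adjusted for it.
- Add emergence from MCS on the CRS-R as a separately named *consciousness recovery* outcome, and use it as the target of the prediction models.

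Then use the same two terms in the Discussion, both for the goal of predicting milestones and in the closing statement of aims.

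No new data are needed, since Table 1 already schedules the CRS-R from T0 to T4. The change does alter the modelled endpoint and its population, so it should be recorded as such. The statistical cost is precision: in the same population everyone who emerges has also moved up, so emergence cannot have more events than any upward step and will usually have fewer. Keeping both outcomes preserves the gradations within DoC that the present rule was meant to capture.
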